## Methods

### Study Design

An exploratory sequential mixed methods design will be used to study the risk perception of midwives and obstetricians. It will first be explored via qualitative data collection and analysis. Second, a quantitative phase will be conducted involving a survey. This design has been chosen to combine the strengths of both quantitative and qualitative research [32].

In phase I the qualitative approach will be applied and narrative data collected via focus group discussions to gain an in-depth understanding of the individual risk perceptions of midwives and obstetricians in the German clinical setting and what they perceive as risky situations. The results of the focus group discussions will assist in determining case vignettes to be used in the second phase to investigate the association of different variables on risk perception and its influence on decision making. In this way, the perceptions and actions of obstetric staff will be documented and evaluated with the help of applicable and everyday case vignettes which reflect the views and personal experiences of the target population and fit the participants being studied [32]. The survey will provide the opportunity for generalization, precision, and investigation of the influence of the obstetric staffs’ risk perception on their intrapartum decision making.

The results will be reported with the Good Reporting of A Mixed Methods Study (GRAMMS) Checklist [33]. Furthermore, the Checklist for Reporting Results of Internet E-Surveys (CHERRIES) [34] is also taken into account.

### Phase I: Focus Group Discussions

A qualitative approach in the form of focus group discussions was chosen in order to conduct a preliminary exploration with midwives and obstetricians and gain insight into their views. Focus groups are not intended to “generalize […] and not to make statements about the population but to provide insights about how people in the group perceive a situation” [35]. Furthermore, focus groups are very well suited when a “range of opinions, ideas or feelings” is looked for or “when opinions or attitudes are conditional or when the area of concern relates to behaviour” [35]. Focus group discussions thus have the advantage of gaining insight into participants’ views in order to capture their voices [32,35]. The evoked discussions create synergies that could not have been achieved to this extent in a one-to-one interview [35]. In addition, group discussions are inexpensive and efficient [35].

#### Recruitment and Sampling

Midwives and obstetricians working in Germany can take part in the focus group discussions. The group composition of the contrasting or comparative groups is based on a sampling plan and on theoretically justified predefined criteria [35]. These predefined criteria have been investigated and described in several studies as possible nonclinical factors influencing clinical performance in general [36] or in the context of childbirth [12,37-41]: age, gender, number of years of experience, type of professional qualification (vocational or tertiary education), and work setting (annual number of births, level of care, care models, eg, midwife-led care/obstetrician-led care). A pool of prospective participants (stratified purposeful sample) will be generated using purposeful sampling strategies, such as typical case sampling and maximum heterogeneity sampling in order to find out which participants “can best help to understand the central phenomena” [32]. The aim will be “to capture major variations rather than to identify a common core, although the latter may also emerge in the analysis” [42]. This approach “represents less than the full maximum variation sample, but more than simple typical case sampling” [42]. Based on the topic under investigation, the predefined criteria will be taken into account to reflect the heterogeneous characteristics of obstetric professionals and, where possible, to assign participants to the different groups. Self-activation and direct contact at specialist congresses, snowball sampling, press releases, and announcements in mailing lists and on the bulletin boards of professional associations in Germany, gatekeepers, and social media platforms, such as Facebook, Twitter, and Instagram, will be used. Inclusion criteria were age (18+) and recent clinical activity: midwives employed by or affiliated with a hospital as an independent midwife; obstetrician/gynecologists employed in an obstetric department; having 1 or more years of professional experience since qualifying; and having good knowledge and understanding of the German language. Freelance midwives with no hospital affiliation or midwives who have not worked in a delivery room within the last 2 years will be excluded. According to Krueger and Casey [35], the ideal size of a focus group is between 5 and 8 participants, so 3-4 focus groups of 5-8 participants are planned.

#### Data Collection and Analysis

Krueger and Casey’s [35] recommendations will be followed such that each focus group discussion will last approximately 60 minutes (maximum 90 minutes). Further, the moderator conducting the focus group discussion will use a questioning route, developed for consistency and including opening, introductory, transition, key, and ending questions [35]. Participants will be asked to answer the following question: “What do you understand by the term ‘risk’ during labor and birth?” and “Which situation(s) in the delivery room do you consider risky?” or “Describe a situation in the delivery room that you associate risk with.”

The focus group discussions will be digitally audio recorded and the recordings transcribed using the software program f4transkript ([name] & Pehl GmbH) [43]. Before the beginning of the discussion, participants will be asked to fill in a short questionnaire to specify demographic data (eg, age, gender, years of professional experience, annual number of births, and level of care of the past and present places of work) for the analysis process. The transcribed data will be analyzed using the software MAXQDA (version 2018.2; VERBI GmbH) according to qualitative content analysis and an analysis plan. This systematic approach includes initial examination of the data, highlighting text passages, writing notes and memos, developing codes, subcodes, and identifying an emerging code system [44,45]. The main author (NP) will be the main person responsible for the analysis process and coding, nevertheless the entire analysis process will be discussed and reflected in the research team meetings; additionally, a peer audit is planned. Discrepancies will be resolved through team discussions and reflection. The results of the focus group interviews will be used to construct case vignettes of risky situations in the delivery room. The case vignettes are intended to highlight the subjective sense of action in which the social reality of the obstetric professionals is produced. The vignettes will be checked by clinicians and experts (clinicians, psychologists, researchers) to assess their face validity in a subsequent evaluation phase and adjusted if necessary. The experts will be recruited from the professional network of the authors. The valid case vignettes will be used in phase II. In this way, qualitative findings will be used to construct the second, quantitative phase of this research project.

### Phase II: Survey

In phase II, a survey (either web-based or paper and pencil) using the case vignettes constructed in phase 1 will be used to study whether different factors such as age, gender, years of experience, annual number of births, or level of care of the clinic have an influence on the risk perception. Furthermore, the association of between the risk perceptions of obstetric health professionals and the decision-making process during intrapartum care will be investigated.

#### Recruitment and Population

Almost the same recruitment strategies and inclusion/exclusion criteria as those outlined above for phase I will be used to invite midwives and obstetricians employed in Germany to participate in the survey. The sample will be a convenience sample. Using the recruitment strategies, it is planned to invite as many midwives and obstetricians to participate as possible.

#### Data Collection and Statistical Analysis

Participants will be asked to fill out a version of either the web-based or paper-and-pencil self-constructed survey containing the vignettes of different birth scenarios. The primary endpoint is the risk perception of obstetric health professionals (midwives and obstetricians) caring for women giving birth measured on a 6-point Likert scale. The primary endpoint is thus ordinally scaled with 6 parameter values (from 0=hardly or no risk to 5=very high/highest possible risk).

As the aim is to invite as many midwives and obstetricians to participate as possible, no formal statistical sample size calculation will be carried out.

The secondary endpoint is the decision to intervene (binary with the variables “intervene yes” and “intervene no”) whereby the decisions are partly predefined as described earlier. On the basis of a 5-point Likert scale (from 1=very unlikely to 5=very likely to choose the intervention), if the score is over 3, the characteristic “intervene yes” will be assumed.

Descriptive presentation of the results of the primary endpoint (categorical; 6 categories) will be displayed through bar charts and associated absolute and relative frequencies. Other additionally recorded variables will be analyzed according to the data situation (continuous, categorical, or binary) using statistical methods appropriate to the data structure (categorial/binary: absolute and relative frequencies; continuous: medians, quartiles, means, standard deviation, minimum, maximum). Exploratory analyses for the primary endpoint (generating hypotheses) will be performed via ordinal regression using SPSS (IBM Inc) or R (R Foundation for Statistical Computing) with the following potential influencing factors: age, gender, type of professional qualification, years of experience, annual number of births or level of care of the current work location, and personality inventories. The choice of the link function to be used for this purpose will depend on the distribution of the observed cases among the different categories of the dependent variable. The quality of the model will be checked by Nagelkerke R^2^. Results of the ordinal regression will be summarized via regression coefficients, corresponding odds ratios, and by determining 95% confidence intervals for the odds ratio.

Descriptive evaluation of the secondary endpoint depending on the risk perception will be carried out using a frequency table with absolute and relative frequencies. Depending on the obtained date, either a table form with a risk perception dichotomized at cut point over 3 or a table form with a risk perception as described in the primary endpoint with 6 variables will be used.

In an additional analysis, the influence of risk perception on the decision to intervene (yes or no) will be done using logistic regression adjusted for the following variables: age, gender, type of professional qualification, years of experience, annual number of births or level of care of the current work location, and personality inventories. The choice of model is made by forward selection using a likelihood ratio test. The quality of the model will be analyzed with Nagelkerke R^2^. Results of the logistic regression are summarized with regression coefficients, corresponding odds ratios, and by determining 95% confidence intervals for the odds ratio.

Continuous data are descriptively evaluated by calculating measures of central tendency (minimum, maximum, quartiles, median, mean) and measures of variation (standard deviation, interquartile ranges, span). Graphical presentation will be made by suitable methods (eg, boxplot, scatter plot).

Categorical and binary data will be represented by calculating absolute and relative frequencies within frequency tables (potentially supported by bar charts). In addition, the risk measures (odds ratio, absolute risk) for group comparisons of interest will be calculated. An optional analysis of the actual power of the resulting models is desired via G*Power [46].

Statistical analysis will be supported by the Institute for Medical Biometry and Epidemiology at the University of Witten/Herdecke. The design and scope of the survey in phase II depend on the results of phase I, so it will be possible to adapt the content and design of the survey as appropriate. A pretest of the survey will be undertaken before fielding the questionnaire with a heterogeneous group of clinicians and research associates using a think aloud protocol and written feedback. In Figure 1 the exploratory sequential mixed methods design of this study is summarized according to Creswell [32].

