In Germany, in general, midwives and obstetricians are involved in the care of women giving birth. According to the legal regulations, a midwife must be present at every birth and therefore all women in labor, regardless of having a low- or high-risk pregnancy, are cared for by midwives. In a low-risk birth without complications the midwife is responsible for the birth process on her own; nevertheless, in hospitals a doctor usually is also present at the actual birth. In a high-risk birth or when abnormalities occur, a doctor must be called and takes charge of the birth, but a midwife still takes care of the woman. There are some midwife-led units where women in labor with a low-risk pregnancy are cared for exclusively by midwives as long as no abnormalities occur [23], but this is rather the exception. However, most births occur in consultant-led obstetric units [2]. Therefore, women giving birth in hospitals are usually interdisciplinary cared for by midwives and obstetricians. Decisions to or not to intervene are made by a midwife alone, by a doctor alone, or together, which depend on the model of care and the circumstances. In Germany, there also are regional variations in the use of interventions. For example, the overall caesarean section rate was 30.2% in 2015 [24], but varied from 19% to 47% in western and eastern districts of Germany [5,6]. Epidurals and augmentation of labor differed significantly in hospitals with lower or higher annual number of births [25]. The high intervention rates and the regional differences lead to the assumption that, in addition to medical indications, other factors influence the decision to intervene. As other researchers showed, these might be the clinicians' personal beliefs, including the risk perception, which was an influencing factor for the choice of the mode of birth, of performing a cesarean section [12]. The association between risk perception and the decision-making processes of health professionals during intrapartum care has not yet been investigated in the German clinical setting. To gain insights into the decision making to use interventions during childbirth is of importance to study because interventions such as administering an epidural agent, intrapartum use of oxytocin, performing an episiotomy or a caesarean section are associated with short- and long term effects such as higher maternal mortality and morbidity (eg, increased risk of uterine rupture, abnormal placentation, sexual dysfunction), less satisfaction with the birthing process, a longer and more costly hospital stay, a longer recovery including the experience of pain and reduced mobility, or stillbirth, preterm birth, and greater incidence of late childhood obesity [7,26-30]. This has led to the tremendous increase in the relative cost of birth within the last century; besides, obstetric interventions during labor for women with a low-risk pregnancy, in general, are costly to the health system [31].

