
It is therefore crucial to gain insight into the risk perception of obstetric health professionals working in Germany so as to investigate the association between risk perception and decision-making processes in the German clinical setting in order to improve intrapartum care in Germany. Overall, in a simplified view, midwives and obstetricians are often assigned to different models of care, with midwives being assigned to the social model focusing on normality and obstetricians to the medical model focusing on technology and pathology. Although more of a continuum, this could be an indication of different approaches and perspectives due to socialization [14]. Therefore, this work focuses on the risk perception of obstetric health professionals in general, but differentiates between midwives and obstetricians to obtain more specific insights.

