### Aims and Research Question

The overall aim of this study is to understand the association between risk perception and the decision-making processes of obstetric health professionals in Germany during intrapartum care. This study has 3 aims: (1) to gain insight into what midwives and obstetricians perceive as risk in the German clinical setting in order to construct valid case vignettes of risky situations; (2) to assess the extent to which personal factors (eg, age, gender, professional experience, qualification level) or systemic factors (eg, annual number of births or level of care provided, ie, secondary or tertiary) have an impact on midwives’ and obstetricians’ risk perception; and (3) to investigate whether differing perceptions of risk are associated with different decisions by midwives and obstetricians.

To this end, the research questions are as follows:

1. What do obstetric health professionals understand by risk in labor in a clinical setting, and which situations are perceived as risky intrapartum?

2. Do personal, systemic, or both factors affect the risk perception of obstetric health professionals?

3. Does risk perception affect the decisions of the obstetric health professionals or the care of women in labor?

The decisions were predefined as administering an epidural agent, intrapartum use of oxytocin, or performing an episiotomy or an unplanned caesarean section. However, adding other decisions based on the results of the first research question remained open.

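### Both Phase II regression models omit profession (midwife or obstetrician), so neither gives an adjusted contrast between the two, and the aim 3 odds ratio is open to confounding by profession

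*Protocol article*

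**What the plan says.** All references are to the protocol article.

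- **Purpose.** The Background says the work looks at obstetric professionals in general but "differentiates between midwives and obstetricians to obtain more specific insights". Its reason is that the two groups are often assigned to different models of care, and "this could be an indication of different approaches and perspectives due to socialization". Aim 3 is "to investigate whether differing perceptions of risk are associated with different decisions by midwives and obstetricians".
- **Primary model.** Under Phase II, Data Collection and Statistical Analysis, the ordinal regression of the 0–5 risk rating is to be run "with the following potential influencing factors: age, gender, type of professional qualification, years of experience, annual number of births or level of care"; the last two refer to the respondent's present workplace, and personality inventories complete the list.
- **Decision model.** The logistic regression of intervene yes/no on risk perception is "adjusted for the following variables: age, gender, type of professional qualification, years of experience", births or level of care, and personality inventories. Its terms are chosen by forward selection with a likelihood ratio test.
- **Meaning of qualification.** Phase I, Recruitment and Sampling, lists "type of professional qualification (vocational or tertiary education" as one of the predefined criteria. Aims and Research Question calls the item qualification level.
- **Other provision.** The same Phase II section promises odds ratios and absolute risks for group comparisons of interest, without naming the groups. It describes no stratification or interaction by profession.

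**The concern.** The article commits itself to named adjustment sets, and these do not match its stated purpose. This is therefore a list fixed badly, not a detail left for a fuller document.

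Two things are at stake.

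- **Aim 2.** Without a profession term, the ordinal model cannot say whether midwives and obstetricians rate the same vignette differently once age, experience and workplace are allowed for. If obstetricians are all coded as tertiary-educated, the qualification coefficient will also mix an education effect with a profession effect.
- **Aim 3.** By the article's own reasoning, profession may shift the risk rating, through socialization into different perspectives. It may also bear on the decision, since "Decisions to or not to intervene are made by a midwife alone, by a doctor alone, or together". A variable linked to both exposure and outcome and left out of the model can bias the odds ratio between them, in either direction.

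**Working it through.** The article gives no sample size, power or effect size, so there is no planned figure to reproduce. The check has two parts.

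**1. Comparing the texts.** The ordinal and logistic lists name the same six items: age, gender, type of qualification, years of experience, births or level of care, and personality. None is profession. The nearest is qualification, and the article's only explanation of that phrase separates vocational from tertiary education. On that coding a tertiary-educated midwife and an obstetrician share a category. Vocational training would identify midwives only if every obstetrician is coded tertiary, which is an assumption. The term therefore captures part of profession, and all of it only if no midwife is tertiary-educated.

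**2. How far the aim 3 odds ratio could move.** Every input here is assumed; none comes from the article.

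- Share of obstetricians: 20%, 35% or 50%.
- Tertiary education: all obstetricians, and 10% or 30% of midwives.
- Rating: mean 2.3 and SD 1.2 in midwives, limited to 0–5. Obstetricians are shifted by +0.5 or +1.0 point, or by −0.5 point.
- Decision: logit P(intervene) = −0.5 + ln(OR) × obstetrician, with OR = 2 or 4. The rating has no effect within either profession, so the true odds ratio per point is 1.00.

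Logistic models were fitted to large simulated samples. The last digit moves with simulation error.

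| Terms besides the rating | Obstetricians rate higher (+0.5 to +1.0) | Obstetricians rate lower (−0.5) |
|---|---|---|
| None | 1.04–1.22 | 0.90–0.96 |
| Qualification, as listed | 1.01–1.12 | 0.94–0.99 |
| Qualification and profession | 1.00 | 1.00 |

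Across the whole scale (score 5 versus 0), the extremes with qualification in the model are 1.12^5 = 1.76 and 0.94^5 = 0.73. The lower end reflects a half-point downward shift only. A full point down would roughly mirror the upper end, at 1/1.12 = 0.89 per point.

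A milder set of assumptions used 20% or 40% obstetricians, a shift of −0.5 to +1.0 on the logit scale of the latent rating, and a profession odds ratio of 1.5 or 3. It gave 0.95–1.10 with no covariate, 0.976–1.050 with qualification and 0.995–1.006 with profession added. The pattern is the same. Qualification removes part of the bias, and adding profession removes it apart from simulation error. If forward selection drops qualification, the estimate moves back towards the first row of the table.

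**The case against.** The strongest reply is that the plan already adjusts for qualification, so a calculation that leaves it out overstates the damage. That stands. The no-covariate figures show where the estimate drifts if qualification is not selected; they are not the expected result of the plan. If no midwife is tertiary-educated, qualification coincides with profession and the bias vanishes.

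A reader might infer more than the text supports:

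- **That aim 3 is in fact confounded.** The article gives reasons to expect links between profession and both variables, but no magnitudes, and the direction is unknown. Open to confounding is as far as it goes.
- **That the professions will not be compared at all.** The clause on group comparisons of interest could cover an unadjusted comparison. It names no groups and adjusts for nothing, so it answers only in part.
- **That who decides is fixed by profession.** The Background ties this to the model of care and the circumstances, and in the survey each respondent states their own intended decision.
- **That a pooled odds ratio is known to mislead.** If the odds ratio per point were 1.6 in obstetricians and 1.0 in midwives, the pooled value would be 1.09, 1.17 or 1.25 at 20%, 35% or 50% obstetricians. Nothing in the article indicates such a difference.
- **That care model must be added too.** The Background calls midwife-led units the exception, so the cell may be sparse and leaving it out is defensible.

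The vocational/tertiary gloss also sits in the Phase I section, and Phase II coding is not spelled out. Carrying the same phrase over is reasonable but remains an inference. Finally, the ordinal regression is labelled exploratory, the logistic one additional, and the survey's content adaptable. This lowers the severity but does not reconcile the lists with the stated purpose.

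**Conclusion.** The point holds in a limited form. Both covariate lists leave out profession, against the article's stated intention to separate midwives from obstetricians, and qualification type is at best a partial stand-in. The models as written provide no adjusted profession contrast for risk perception, and the odds ratio of risk perception on the decision is open to confounding by profession.

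The size cannot be known from the article. Under the assumed ranges, with qualification retained and no true association, the odds ratio lies at roughly 0.94–1.12 per point, moving towards 0.90–1.22 if qualification is dropped. This is a modest distortion per point but not negligible across a six-category scale. It matters most if the true association is weak. It should be fixed, but it does not invalidate an exploratory study.

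**What to change.** - Add profession (midwife or obstetrician) to the covariate lists of both the ordinal and the logistic regression.
- Force it into the logistic model instead of leaving it to forward selection.
- Report the risk-perception odds ratio by profession as well, labelled exploratory.
- State how type of professional qualification is coded in Phase II, so that it is not mistaken for profession.

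The change is to wording. Eligibility is defined separately for midwives and obstetricians, so profession has to be established for every respondent; it need only be kept as a survey variable. The statistical cost is one or two more parameters and a wider interval for whichever profession is less well represented.

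### The aim 3 logistic model has a listed adjustment set but is chosen by forward selection, so listed confounders can be left out and the 95% intervals ignore the selection

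*Protocol article*

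**What the plan says.** All of this is in the protocol article. In Phase II, Data Collection and Statistical Analysis, the model for the secondary endpoint is introduced as follows: "the influence of risk perception on the decision to intervene (yes or no) will be done using logistic regression adjusted for the following variables". The list comprises age, gender, professional qualification, experience, annual births or level of care at the workplace, and personality inventories. The next sentence reads: "The choice of model is made by forward selection using a likelihood ratio test". No entry threshold is given and no term is said to be forced in. The output is then described: "Results of the logistic regression are summarized with regression coefficients, corresponding odds ratios, and by determining 95% confidence intervals for the odds ratio".

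Two other places bear on this. The third aim, in Aims and Research Question, is "to investigate whether differing perceptions of risk are associated with different decisions by midwives and obstetricians". The ordinal regression for the primary endpoint models risk perception itself, scored "from 0=hardly or no risk to 5=very high/highest possible risk", "with the following potential influencing factors: age, gender, type of professional qualification, years of experience" and the remaining listed variables. No selection step is stated for that model.

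**The concern.** Aim 3 asks for the effect of one named exposure, adjusted for named variables. A fixed adjustment set and forward selection cannot both define that model: the first puts every listed variable in, while the second admits only those that pass an in-sample test.

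Forward selection screens a covariate on its association with the outcome, given the terms already chosen, and takes no account of its association with risk perception. A covariate that drives risk perception and has a modest effect on the decision is a confounder, and it is also a term that such a test easily misses. The article's own ordinal regression treats the same variables as possible influences on risk perception, so they are plausible confounders here. If some fail to enter, the reported odds ratio is not adjusted for the stated set. Its interval is then computed as though the model had been fixed in advance.

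**Working it through.** The document gives no sample size, effect size or entry threshold, so there is no figure to reproduce. The check has two parts: reasoning from the text, and simulation under stated assumptions.

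**1. What omission does.** Let a listed covariate have coefficient γ for the decision, and let δ be its slope on risk perception given the retained terms. Leaving it out shifts the risk-perception coefficient by about γ × δ (a linear approximation). The sign depends on both factors, and the document gives neither.

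**2. First simulation.** 1,000 runs per cell; none of these inputs comes from the document.
- Ten covariates: age, experience (correlated 0.85 with age), gender, qualification, level of care and five personality scores. Four are confounders: experience, qualification, level of care and one personality score.
- Risk perception R is 2.5 + 1.2 × noise − 0.4 × experience + 0.5 × qualification + 0.5 × level + 0.3 × personality (qualification and level centred), rounded and limited to 0–5.
- The logit of intervening is −0.3 + β(R − 2.5) − 0.3 × experience + 0.4 × qualification + 0.4 × level + 0.25 × personality. Every γ × δ is therefore positive.
- A term enters if the likelihood ratio test has p < 0.05. The interval is b ± 1.96 × SE.
- β is 0, 0.1, 0.2 or 0.4 per point, and n is 150, 300 or 600.

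Risk perception is forced in and only the covariates are selected, which is the reading kindest to the plan. Each model column gives coverage of the 95% interval and the mean estimate of β. The last column counts runs in which at least one confounder was missing, with age accepted as a stand-in for experience.

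| β | n | Full model | Selected model | Confounder missing |
|---|---|---|---|---|
| 0 | 150 | 95.7%, −0.009 | 87.5%, 0.075 | 99.3% |
| 0 | 300 | 94.2%, 0.002 | 84.9%, 0.059 | 95.3% |
| 0 | 600 | 95.7%, −0.003 | 90.1%, 0.021 | 70.3% |
| 0.2 | 150 | 94.5%, 0.217 | 89.2%, 0.288 | 99.6% |
| 0.2 | 300 | 95.5%, 0.207 | 88.0%, 0.259 | 95.1% |
| 0.2 | 600 | 95.6%, 0.201 | 91.0%, 0.221 | 70.2% |
| 0.4 | 150 | 94.0%, 0.442 | 88.6%, 0.503 | 99.5% |
| 0.4 | 300 | 95.1%, 0.420 | 87.1%, 0.468 | 96.4% |
| 0.4 | 600 | 94.4%, 0.412 | 90.4%, 0.434 | 78.0% |

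Over all twelve cells, including β = 0.1, coverage is 94.0% to 95.7% for the full model and 84.9% to 91.0% after selection. With no true effect, the false-positive rate after selection is 100 − 87.5 = 12.5%, 100 − 84.9 = 15.1% and 100 − 90.1 = 9.9% at the three sample sizes, against a nominal 5%. Monte Carlo error is about √(0.85 × 0.15/1000) = 1.1 points.

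**3. Varying the direction of confounding.** A second set of runs (200 to 300 per cell) again used ten covariates, entry at p < 0.05, risk perception forced in and n from 150 to 600, with log-odds ratios of 0, 0.148 and 0.4.
- All confounders acting in one direction: coverage 72% to 81%, with clear upward bias.
- Confounders of mixed sign: coverage 85% to 90%, mean estimates within about 0.03 of the truth.
- Covariates unrelated to risk perception: coverage 92% to 96%, essentially as good as the full model.
- Full model: coverage 91% to 97%. Monte Carlo error at 200 runs is √(0.95 × 0.05/200) = 1.5 points, which accounts for most of that spread.

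Taken together, selection gives about 72% to 96%, and the full model about 91% to 97%.

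**The case against.** The strongest reply is that the size of the problem is assumed. That stands: sample size, effect, correlations and confounding strength are all missing from the document, and if the covariates are unrelated to risk perception, selection does almost no harm. The age–experience correlation is likewise an assumption, and if the two are near-duplicates it matters little which one enters.

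A reader might infer that risk perception itself will be selected away. The document does not support that as fact. It names risk perception as the influence under study and the others as adjusters, so selection among the adjusters is a natural reading. Equally, it does not say that risk perception is kept. If it did compete for entry in the first simulation, it would be left out in 52% to 71% of runs at a log-odds ratio of 0.1 and 13% to 48% at 0.2. Those figures hold only under that reading.

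A reader might also infer that the estimate will be biased away from the null. The first simulation shows upward bias because its confounders all act in one direction; with mixed signs the mean estimate is close to the truth.

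Nor would aim 3 go unanswered. The section also plans a frequency table of decisions by risk perception, and odds ratios and absolute risks for group comparisons, although these are unadjusted.

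Finally, this is called an additional analysis, of a secondary endpoint, in a convenience sample. That limits the consequence. However, the hypothesis-generating label is attached to the primary-endpoint regression, and no such label settles which model is fitted. An unseen analysis plan could add a threshold or forced terms, but the article states the selection rule outright, so the conflict is not mere silence.

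**Conclusion.** Wrong as written. The stated adjustment set and the stated selection rule describe different models. Following the rule, plausible confounders can be left out, and the reported intervals take no account of the selection. Two conclusions need no simulation: adjustment for the listed set is not guaranteed, and neither is 95% coverage. The size does rest on assumptions. With risk perception forced in, coverage was about 72% to 96%, against about 91% to 97% for the full model, for ten covariates, entry at p < 0.05 and 150 to 600 respondents. The direction of bias cannot be determined from the document.

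**What to change.** Delete the forward-selection sentence for this model and replace it with the following.
- Fit one prespecified logistic model with risk perception and all listed adjustment variables forced in.
- Decide between annual number of births and level of care before looking at the data, since the list leaves that open.
- Report the unadjusted and fully adjusted odds ratios with 95% confidence intervals side by side.
- If a selected model is still wanted, label it supplementary and exploratory, with a caveat that its intervals ignore the selection.

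The cost is one replaced sentence and slightly wider intervals. In the smallest simulated sample the full model also showed a small upward bias of its own (mean 0.442 for a true 0.4 at n = 150), less than the selected model's 0.503. By the article's account phase II data collection had not begun, so the change can still be made in advance.
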